## Methods

### Design

The proposed study is a prospective, randomised controlled trial (RCT). The subjects will be randomized to one of the three conditions: (1) brief sex counselling, (2) intensive sexological treatment, and (3) a delayed treatment (waiting list). The trial flow of the proposed subject enrolment and randomization procedures are graphically shown in Figure 1. This study has been approved by the ethics committee academic hospital Maastricht/Maastricht University, the Netherlands. Embedded in this RCT will be a trial-based economic evaluation to investigate the cost-effectiveness and cost-utility of brief sex counselling versus intensive sexological treatment (*see *Figure 1).

**Figure 1 F1:**
[figure not shown]
**Trial flow proposed participants enrolment and randomization procedures**. PHS*: Public Health Service, GP**: General Practitioner.

### Participants

The patient population we aim to investigate consists of adolescents with sexual problems. Patients are eligible to participate if they meet the following criteria: age between 18 and 25 years old; at least mild to moderate sexual problems (based on Questionnaire for the Screening of Sexual Dysfunction [29,30], International Index of Erectile Function (men) [31] and Female Sexual Functioning Index (female) [32]); no severe psychiatric co-morbidity or relational problems, and the sexual problems are not caused by disease, medication use or physical disabilities.

### Interventions

#### Brief sex counselling

Brief sex counselling is a brief, free of charge and easily accessible treatment for sexual problems of people between 18 and 25 years of age. In a maximum of three sessions, of 45 minutes each, a sex counsellor attempts to solve the problems or refers to more specialized help. The treatment is aimed at people without relationship and/or psychiatric problems. The sessions include providing information, psycho-education and limited advice on behaviour change. Furthermore home exercise assignments can be given, and the experiences with these exercises are discussed. The possibility for adolescents to talk about their sexuality in a non-threatening environment could initiate the problem-solving process.

#### Intensive sexological treatment

In a maximum of 10 treatment sessions a (Dutch Association for Sexology) certified sexologist offers an intensive form of treatment for the sexual problem(s) of the participant. This is the standard format of care for adults with sexual problems. In contrast to brief sex counselling, intensive sexological treatment also addresses the relational and/or personal psychological problems which possibly underlie the base of the sexual problems. The treatment is largely based on cognitive-behavioural therapy. In many cases homework assignments have to be carried out. The participant is taught to recognize and change thoughts which could play a negative role in their sex life.

#### Delayed treatment

In the event of the participant being randomized into the waiting list, a period of 26 weeks follows in which no treatment is offered. Participants are requested not to engage in other types of professional treatment. At the end of the waiting list period the participant can choose between brief sex counselling and the intensive sexological treatment.

### Protocol

The protocol that has been developed for the brief sex counselling sessions is based on the principles and practice of sex counselling in general and on a guideline that was developed for the Sense sessions [33,34]. The protocol chapters address problems of sexual desire, sexual arousal, orgasm and sexual pain. First, a description of the disorder is given. Next, specific questions are provided for sexual history taking. Furthermore an action plan is provided. Most of the time is spent on the action plan. This describes what has to be or can be done to solve the problem. The first step in the plan is providing information. This is done to improve the client's knowledge about the cause of his or her problem and the factors that maintain it. A second action point concerns cognitive and behavioural aspects. Several compromised cognitive processes and deficient coping strategies can underlie the sexual problems. During the sessions an attempt is made to identify, change and adjusted these processes and strategies. The protocol provides examples of these processes and strategies and how to deal with them. The last action point concerns teaching of sensate-focus exercises. These exercises aim to help a person or couple to (re)discover sexual needs and preferences. Different exercises provided are tailored to address different sexual problems.

### Research Questions

Both for the effectiveness study as well as for the economic evaluation study we have defined a number of research questions:

#### Effectiveness study

1. Does brief sex counseling as envisaged, when compared to delayed treatment, improve the sexual and general mental health of adolescents and young adults? To which extent (effect size) and in what respect (which outcome dimensions)?

2. Is brief sex counseling efficacious, when compared to delayed treatment, in preventing escalation of (sexual and mental) health problems compared with no help?

#### Economic evaluation

1. Is, from a social perspective, the delivery of brief sex counselling compared to intensive sexological treatment, preferable in terms of costs, effects and utilities?

a. What are the (extra) costs of the delivery of brief sex counselling compared to intensive sexological treatment and waiting list group?

b. What are the (extra) effects (measured in health status and quality of life) of brief sex counselling compared to intensive sexological treatment and waiting list group?

### Outcome measures

Several instruments will be used to assess the effects of brief sex counselling on sexual functioning, depression and other psychological and physical complaints, and on secondary outcomes. Furthermore instruments will be used to assess the cost-effectiveness of brief sex counselling from a social perspective. The outcomes will be measured before randomization (during initial screening), at baseline and at 3, 6, 9 and 12 months after baseline (Additional file 1).

#### Sexual functioning

##### Questionnaire for the Screening of Sexual Dysfunctions

The Questionnaire for the Screening of Sexual Dysfunctions (QSSD) [29,30] is a self-report instrument with 70 items, each assessed using a 5-point or a 7-point Likert-scale, which aims to measure the presence (and level) of sexual difficulties. This instrument has different versions, dependent on gender, partnered status and gender of the partner. Anchor points used are 'almost never' and 'always' for frequency and 'no trouble' and 'very much trouble' for associated distress.

##### Female Sexual Functional Index

The Female Sexual Functional Index (FSFI) [32] is a multidimensional self-report instrument with 19 items, with responses assessed using a 6-point Likert-scale, which aims to measure sexual functioning on the dimensions of sexual desire, arousal, lubrication, orgasm, satisfaction and pain. High score indicates healthy sexual functioning. Its sound psychometric properties have been proven [35].

##### International Index of Erectile Function

The International Index of Erectile Function (IIEF) [31] is a multidimensional self-report instrument with 15 items, assessed using a 6-point Likert-scale, meant to measure male sexual functioning on the dimensions of erectile functioning, orgasmic functioning, sexual desire, intercourse satisfaction and overall satisfaction. A high score indicates healthy erectile functioning. Its sound psychometric properties have been proven [31].

#### Depression and psychological/physical complaints

##### Center for Epidemiologic Studies Depression Scale

The Center for Epidemiologic Studies Depression Scale (CES-D) [36] is a self-report instrument with 20 items, assessed using a 4-point Likert-scale, meant to measure depressive symptoms on the dimensions somatic-retarded activity, depressed affect, positive affect and interpersonal affect. People with a score of 16 and higher can be identified as "possible cases". Several studies have demonstrated sound psychometric properties [36,37].

##### Brief Symptom Inventory

The Brief Symptom Inventory (BSI) [38] is a self-report instrument to measure psychological distress, with 53 items assessed using a 5-point Likert-scale. The dimensions measured are the same as its predecessor the Symptom Checklist-90. The total score of the BSI can be used as an index of severity for general psychological distress (score range 0-212). Several studies have demonstrated sound psychometric properties [39,40].

##### Medical Outcomes Study 36-item Short Form Health Survey

The Medical Outcomes Study 36-item Short Form Health Survey (SF-36) [41] is a self-report instrument with 36 items, assessed using a 5-point Likert-scale, meant to measure the quality of life. Eight dimensions can be identified: physical functioning, role disabilities caused by physical health problems, pain, general health perception, vitality, social functioning, role disabilities caused by emotional problems, and mental health. These eight dimensions can be summed in a physical and a psychological dimension score. Several studies have demonstrated sound psychometric properties [42,43]. Within the cost-utility analysis, utilities will be derived. The term utility refers to the preferences individuals or society may have for any particular set of health outcomes [44]. The patient's health status will be measured with the SF-36; the Short Form 6D will be used to calculate utilities that incorporate preferences from a general population sample

##### Assessment of DSM-IV Personality Disorders questionnaire

The Assessment of DSM-IV Personality Disorders questionnaire (ADP-IV) [45] is a self-report instrument with 94 items, assessed using a 7-point Likert-scale, meant for a categorical and dimensional measurement of the DSM-IV personality disorders. Several studies have demonstrated sound psychometric properties [46].

#### Economic evaluation

The economic evaluation will be performed from the societal perspective. At the cost side we distinguish three cost-categories: health care sector costs, costs for the patient and family, and productivity costs. For this study we will develop a cost questionnaire especially designed for this group, based on existing questionnaires [25,47], which will identify all relevant cost aspects. To measure the actual use of resources data will be obtained using combined sources (registrations by professionals and cost questionnaire). For the measurement of production losses, the patient modules of the PROductivity and DISease Questionnaire (PRODISQ) will be used [47-49]. Productivity costs will be calculated by means of the friction cost method, based on a mean added value of the Dutch working population. This method takes into account production losses confined to the period needed to replace a sick employee [49].

#### Secondary outcomes

##### Credibility/Expectancy Questionnaire

The Credibility/Expectancy Questionnaire (CEQ) [50] is a multidimensional self-report instrument with 16 items, using on a 9- or 10-point Likert-scale, meant to measure the expectancy and credibility a person has about the therapy received. Its sound psychometric properties have been proven [51].

##### Self-Esteem and Relationship Questionnaire

The Self-Esteem and Relationship Questionnaire (SEAR) [52] is a self-report instrument with 14 items, assessed using a 5-point Likert-scale, meant to measure sexual relationship and psychosocial factors specific for people with sexual problems. Two domains can be distinguished; sexual relationships and confidence. High scores indicate problems with regards to the participant's sexual relationship and confidence. Its sound psychometric properties have been proven [52].

##### Treatment Satisfaction Questionnaire

The Treatment Satisfaction Questionnaire (TSQ) is a new instrument, derived from the Erectile Dysfunction inventory of Treatment Satisfaction (EDITS), and adjusted so it would fit the total study population [53]. This instrument measures the satisfaction of the participants with the treatment as a whole and the different aspects of the treatment. The reliability and validity of de EDITS were well established.

##### Demographic and Biographic Questionnaires

Demographic and biographic questionnaires will be used to assess general information like gender, place of birth, age, occupation, but also the use of medication, drugs and/or alcohol, as well as medical and psychological problems.

### Sample size

In a repeated-measures analysis of the within-between-interaction effect, a sample size of 95 in each group has a power of 95% to detect an effect size of 0.41 using repeated-measures MANOVA with a 0.050 two-sided level of significance. In the absence of published controlled studies on professional care for young people with sexual problems, we set the desired effect size at d = 0.40, representing the central point of the range of effect sizes that are considered as 'medium size' [54]. N = 150 per condition is deemed necessary to guarantee the required number of respondents, in view of the expected non-response after inclusion and later attrition [55]. In a repeated-measures analysis of the within-subjects effect, a sample size of 86 in the treated group has a power of 95% to detect an effect size of 0.25 using a repeated-measures MANOVA with a 0.050 two-sided level of significance. The before mentioned N = 150 per condition is expected to guarantee the required number of participants.

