### Analyses

#### Clinical analyses

Our primary (base-case) analyses will be performed according to the intention-to-treat principle, including data from all participants regardless of whether they received the intervention or not. For the analyses we will use SPSS statistical software and Excel (for the bootstraps). Respondents for whom at least 75% of the data per measurement instrument are available will be included in the analysis. Missing data on item level will be handled using SPSS missing value analysis. Completely missing measurements will be handled using multiple imputation. Analysis will include comparisons of the intervention groups (brief sex counselling, sexological treatment and waiting list) as well as more complicated multi-level analysis. The accuracy of the findings will be expressed in terms of 95% confidence intervals.

To test the main research questions, difference scores for all outcome variables will be calculated and compared between the three intervention groups using MANOVA. In the case of significant multivariate results, subsequent univariate analysis using independent groups t-tests will be conducted to assess the significance of differences pre/post intervention between control and experimental groups.

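### The 95% power quoted for 95 per group is not supported for the stated target (d = 0.40) and the planned difference-score analysis; it depends on an unstated correlation or a different effect-size metric

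*Protocol article*

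**What the plan says.** For the group-by-time interaction, the Sample size section of the protocol article states: "a sample size of 95 in each group has a power of 95% to detect an effect size of 0.41 using repeated-measures MANOVA". The test is two-sided at 5%. The section does not say whether 0.41 is a standardised mean difference or an f, and gives neither the number of occasions nor the correlation between them. The following sentence reads: "we set the desired effect size at d = 0.40". On enrolment it says: "N = 150 per condition is deemed necessary to guarantee the required number of respondents". A second calculation gives 86 treated participants, effect size 0.25 and again 95% power for a within-subjects effect.

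The Clinical analyses section describes the test of the main questions: "difference scores for all outcome variables will be calculated and compared between the three intervention groups using MANOVA". If the multivariate result is significant, independent-groups t-tests on the pre/post differences follow. Multi-level analysis is mentioned without detail. Both effectiveness questions compare brief counselling with delayed treatment, a two-group contrast.

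**The concern.** Power is quoted at 0.41 but the target is 0.40. No assumption is needed to see that these differ, or that the smaller effect has the lower power. More importantly, 95 per group is exactly the smallest two-group t-test size that gives 80% power at d = 0.41, and the t-test on differences is where the planned analysis ends. The 95% might therefore belong to another test, another effect-size metric, or a total rather than a per-group count.

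The stake is how a null result is read. A reader who accepts 95% will take a non-significant difference between brief counselling and delayed treatment as good evidence against a medium effect. If power is nearer 78%, the type II error is about 22% rather than 5%.

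**Working it through.** **Inputs.** From Sample size: n = 95 per group, effect 0.41, target d = 0.40, two-sided alpha 0.05, 150 randomised per group (95/150 = 63% retained). From Design: three groups. From Outcome measures: baseline plus four follow-ups. The correlation ρ between occasions is not given, so every value of it below is an assumption.

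**1. Planned t-test on difference scores.** Noncentral t with df = 2n − 2 and noncentrality d·√(n/2), d on the difference-score SD.
- n = 95, d = 0.41: 0.41 × √47.5 = 2.83; power 80.3%.
- n = 95, d = 0.40: 0.40 × √47.5 = 2.76; power 78.3%.
- n = 94, d = 0.41: 79.9%, so 95 is the smallest n reaching 80%.
- 95% power needs 156 per group at 0.41 or 164 at 0.40. Both exceed the 150 randomised.
- With all 150 analysed: 94.3% at 0.41 and 93.2% at 0.40.
- With 95 per group, 95% power corresponds to d = 0.53.

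**2. Can the stated 95% be reproduced as a pre/post interaction with d on the raw SD?** The effective effect is d/√(2(1 − ρ)), then as in step 1 with n = 95. This is identical to the 2 × 2 repeated-measures interaction test.

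| Assumed ρ | d = 0.41 | d = 0.40 |
|---|---|---|
| 0.3 | 66% | 64% |
| 0.5 | 80% | 78% |
| 0.7 | 95% | 94% |

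The 95% is reached at ρ of about 0.70 for 0.41 and about 0.71 for 0.40.

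**3. Can it be reproduced with 0.41 as the MANOVA f(V)?** For 3 groups × 2 occasions or 2 groups × 3 occasions, the interaction F has 2 and N − 3 degrees of freedom, with noncentrality f²·N, where N is the total.
- N = 95 in total: 0.41² × 95 = 15.97; power 95.0%. This is the smallest such N.
- 95 per group (N = 285 or 190): over 99.9%.
- In two groups d = 2f, so f = 0.41 corresponds to d = 0.82, against the stated 0.40. Conversely, d = 0.41 gives f = 0.205, the case already covered in step 1.

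**4. The companion figure (86, 0.25, 95%).** Within-subjects test with noncentrality f²·n·m/(1 − ρ), where m is the number of occasions.
- Read as f with m = 3, ρ = 0: 0.0625 × 86 × 3 = 16.1; power 95.1%.
- Read as f with m = 2, ρ = 0.2: 0.0625 × 86 × 2/0.8 = 13.4; power 95.2%.
- Read as a paired d: 0.25 × √86 = 2.32; power 63%.

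Read as an f, this figure fits a correlation of 0 to 0.2, not the 0.70 that the first figure needs when read as a raw-SD d. The trial has five assessments, not two or three.

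**The case against.** The strongest reply is that the article ties its 95% to a repeated-measures interaction. A t-test calculation does not refute a figure computed for another test, and the t-tests come only after a significant multivariate result. The figure is attainable: a pre/post interaction reaches it at ρ of about 0.70, and baseline against the mean of four follow-ups, under compound symmetry at ρ = 0.5, gives 94.5% at 0.41 and 93.4% at 0.40. Read as f(V), 95 per group is more than enough. The step from 0.41 to 0.40 alone costs only about 2 percentage points. A condensed article may also leave the correlation and the number of occasions to the full protocol.

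Much of this stands. A reader might infer that 95% is simply wrong and 80% is the truth, or that the trial is underpowered. The documents do not support either, because the correlation and the metric are open. Nor do they establish that a total was miswritten as a per-group number: 95 also happens to be the 80% size for the t-test, so a numerical match is not a diagnosis. Leaving out the correlation would not by itself be a finding.

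What the reply does not do is make the paragraph consistent. The four-follow-up contrast is not the pre/post comparison described in Clinical analyses. It also mixes untreated and treated time in the control arm, since delayed-treatment participants may choose treatment after 26 weeks. The f reading conflicts with the target d, and the d reading needs a favourable correlation that the article never states.

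**Conclusion.** The 95% is not supported for the stated target and planned analysis. With 95 evaluable per group and d = 0.40, power for the difference-score t-test is about 78% if d is on the difference-score SD, or on the raw SD with ρ = 0.5. On the raw SD it runs from 64% (ρ = 0.3) to 94% (ρ = 0.7), and reaches 95% only at about 0.71 or above. If 0.41 is an f(V), the calculation fits 95 participants in total and an effect about twice the stated target. The calculations assume equal groups, two-sided 5%, and normal outcomes with equal variances. The range of ρ is illustrative. The mismatch between 0.41 and 0.40 rests on no assumption.

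**What to change.** - Recompute and restate the power for brief counselling versus delayed treatment at one effect size, d = 0.40. Name the metric (raw or difference-score SD), the contrast, the occasions, and the assumed correlation with a range. At this n the statement would be about 78% at a correlation of 0.5, and 95% only at about 0.71 or above. Justify whichever correlation is adopted; 0.5 is used here only for illustration.
- Check the original calculation to see whether 95 was a total and whether 0.41 was an f.
- State the occasions and correlation behind the 86-participant figure, or reconcile it with the planned between-group analysis.

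The cost is one recalculation and a rewritten paragraph. No extra enrolment is needed. The downside is that the stated power is likely to look less favourable.

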### Randomisation and procedure

For this study a block randomisation procedure will be used to ascertain that each intervention runs in equally large groups. Although the order of the interventions varies randomly within each block, a person running the trial could deduce some of the next treatment allocations if they discovered the block size. In this study we use larger block sizes (30) and randomly vary in block size which can ameliorate this problem [55]. Allocation will be performed by a central independent research assistant after getting informed consent, screening, and checking the in- and exclusion criteria, using Schouten's (1995) adaptive biased urn randomization for small strata. This keeps randomization unpredictable up to and including the last participant on each site, while keeping the group sizes at each site in good balance [56].

The questionnaires will be administered using a computer. All assessments will take place at home via internet. Preceding an upcoming assessment point, participants will receive an email (one week before the end of the treatment and 3 months after the start of the follow-up measurement). If a participant fails to complete the assessment within one week, an email-reminder will be sent. When the participant fails to fill in the questionnaires, a phone call will be made.

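### The protocol names two incompatible procedures, permuted blocks and an adaptive biased urn by site, for one and the same allocation step

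*Protocol article*

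**What the plan says.** All statements on the allocation method stand in one paragraph of the protocol article, under Randomisation and procedure.

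- **Blocks.** "For this study a block randomisation procedure will be used to ascertain that each intervention runs in equally large groups". The mechanism is a permuted block: "Although the order of the interventions varies randomly within each block". The section concedes that someone who learned the block size could work out some upcoming allocations, and answers that "we use larger block sizes (30) and randomly vary in block size". No strata are named.
- **Urn.** A central independent research assistant then allocates, after consent, screening and eligibility checks, using "adaptive biased urn randomization for small strata". The property claimed is: "This keeps randomization unpredictable up to and including the last participant on each site, while keeping the group sizes at each site in good balance".

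The Design section gives three arms and the Sample size section 150 per arm. The Recruitment section lists several public health services, Sense and websites as routes of entry. Under Clinical analyses, the main comparison is a MANOVA on difference scores followed by independent-groups t-tests. No stratification factor is named for it, although multi-level analysis is also mentioned in general terms.

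**The concern.** A permuted block and an adaptive urn generate allocations in different ways. A block draws from a sequence with fixed arm totals. An urn draws each allocation at random and then updates the probabilities. A given participant's arm can come from only one of them. The article does not assign them to different stages, sites or levels, does not make one a fallback, and does not describe a hybrid.

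Three things depend on the answer:

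- which balance is promised: equal arms overall, or good but inexact balance within each site;
- whether the claim of unpredictability through the last participant is true;
- which strata the analysis should respect.

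**Working it through.** The plan states no figure that depends on this point, so there is none to reproduce. The check sets the two descriptions side by side and asks whether one sequence can satisfy both.

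**1. The stated features**

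| Feature | Blocks | Urn |
|---|---|---|
| Mechanism | random order within a block | probabilities adapted as allocation proceeds |
| Strata | none named | site |
| Balance claimed | equally large groups | good balance at each site |
| Predictability | some allocations deducible if the block size is discovered | unpredictable through the last participant on each site |

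**2. What blocks imply.** Inputs: three arms (Design), 450 participants (3 × 150, Sample size), block size 30 (the only size given).

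- Arms per block: 30/3 = 10 each. Number of blocks if all were of size 30: 450/30 = 15, with no remainder.
- Each completed block is exactly balanced. After 29 of its 30 allocations two arms stand at 10 and one at 9, so the 30th must go to the third arm. The same holds for any block size: the last place is whatever the earlier ones have left.
- The property in "This keeps randomization unpredictable up to and including the last participant on each site" therefore cannot be claimed for a sequence made of completed permuted blocks.

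**3. What an urn implies.** The article gives no urn settings. As an illustration, a generic three-arm urn was simulated under assumed settings: 1 or 5 starting balls per arm, and 1 or 3 balls added to each arm not drawn.

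| n | Largest final probability of any arm | Runs with exactly equal arms | Mean gap, largest minus smallest arm |
|---|---|---|---|
| 30 | about 0.45 | 4.1% to 5.5% | 3.8 to 4.2 |
| 450 | about 0.36 | 0.25% to 0.5% | 14.3 to 14.7 |

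At the end of these runs no allocation was certain, and exact equality was rare. The urn that the protocol cites may balance better than this generic one. The qualitative result does not depend on the settings: if every draw keeps more than one possible outcome, equal arms cannot be guaranteed.

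**4. Together.** Exact balance from completed blocks requires determined allocations, and unpredictability through the last participant rules them out. One sequence cannot deliver both.

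**5. Consequence for the analysis.** Suppose allocation is balanced by site and a share ρ of the outcome variance lies between sites. Under close balance the site differences cancel from the difference between arm means, so its true variance is about 2σ²(1 − ρ)/n. A t-test that ignores site estimates about 2σ²/n. The standard error is then too large by a factor of about 1/√(1 − ρ). The article gives no ρ, so the amount cannot be stated. The direction is conservative.

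**The case against.** The strongest defence is that a central assistant running one program would in practice follow one algorithm, and that the article merely describes it loosely. Central allocation after eligibility checks also limits the scope for prediction under either method. Both points are fair, and they keep this a matter of clarification. They do not tell the reader which algorithm it is.

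It can also be said that a hidden, varying block size makes the last place in a block hard to guess even though it is determined. That is true in practice. But the section itself says only that varying the size can ameliorate the problem, whereas the urn claim carries no such condition.

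Four stronger readings are tempting and are not supported:

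- **That allocation would be seriously predictable.** A calculation with a fixed, known block of 30 and a guesser who sees every earlier allocation gives a worst case. The text plans against it through varying block sizes and central allocation.
- **That the urn is the better choice.** Nothing in the article shows this. In a site of 15, an arm gap of 4 or more arises in about 26% to 27% of cases with blocks of 30, and in 27% to 35% with the generic urn under the assumed settings.
- **That sex must be a stratum because the FSFI and IIEF are sex-specific.** The article claims no stratification by sex, so it contradicts nothing here. Adding it would be a design preference.
- **That the planned tests would be invalid.** Ignoring a balanced factor costs precision and does not inflate false positives. The mention of multi-level analysis also means that site may enter some planned models.

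The block size given as 30 and also as varying is at most loose wording. It can be read as large blocks with 30 as an indicative size, and the exact sizes can reasonably stay in a fuller document.

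**Conclusion.** The contradiction is real and rests on the text alone. Two mechanisms are stated for one allocation step, with different strata and with properties that exclude each other. This is not detail left to a fuller protocol, because the article affirms both.

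Its weight is moderate. The allocation method, its strata and the truth of the unpredictability claim cannot be established from the article, and the main comparison does not name the factor by which the urn text balances. Planned sample size and power are unaffected. The conclusion on exclusive properties needs no assumption beyond the definitions of the two mechanisms. The urn figures rest on assumed settings and only illustrate. The precision loss assumes that allocation is in fact balanced by site and that outcomes differ between sites.

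**What to change.** 1. Keep one procedure; either is acceptable. Delete the other together with the properties claimed for it. If blocks are kept, remove the claim of unpredictability through the last participant. If the urn is kept, remove the block sentences and describe the arms as approximately equal in size. If a combination is truly intended, say which procedure applies where.
2. State the strata. If site is one, define it and say how a participant recruited through a website is assigned to a site.
3. If allocation is balanced by site, include site as a factor in the MANOVA on difference scores, and replace the follow-up t-tests by between-arm comparisons adjusted for site.

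The cost is a rewritten paragraph and one model term. The model loses a few degrees of freedom (number of sites minus one), which is small against 150 per arm. If the urn is kept, the price is arm sizes that are not exactly equal.
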